## Figures and Tables

**Figure 1 ijerph-23-00504-f001:**
[figure not shown]
Adapted CONSORT flow diagram of the intervention under the immersive virtual reality protocol.

**Figure 2 ijerph-23-00504-f002:**
[figure not shown]
Oculus Meta Quest 3s headset and controllers.

**Figure 3 ijerph-23-00504-f003:**
[figure not shown]
Views of the Boxing Game mode in Oculus Meta Quest 3s. (**A**) First-person view during gameplay in mixed reality in a static position. (**B**) First-person view during gameplay in mixed reality in dynamic movements.

**Figure 4 ijerph-23-00504-f004:**
[figure not shown]
Views of “Gym 360” exercises of Balance. (**A**) Point of view professional exercises of balance 1 and 2. (**B**) Point of view professional exercises of balance 3 and 4.

**Figure 5 ijerph-23-00504-f005:**
[figure not shown]
Views of exercises on Activities of Daily Living (ADL) on KINESIX XR. Point of view professional on vestibular exercises.

**Figure 6 ijerph-23-00504-f006:**
[figure not shown]
Views of exercises on Activities of Daily Living on KINESIX XR. First-person view exercises of AVD.

**Figure 7 ijerph-23-00504-f007:**
[figure not shown]
A quasi-experimental Virtual Reality-Based Program for Fall Risk Reduction in Older Adults in Primary Health Care.

**Table 1 ijerph-23-00504-t001:** Inclusion and exclusion criteria.

Inclusion Criteria	Exclusion Criteria
○ Age ≥ 60 years.	○ Progressive neurological diseases or major neurocognitive disorders.
○ Functional status classified according to EFAM and the Barthel Index: autonomous older adults without risk or with mild risk of dependency.	○ Uncompensated sensory impairments.
○ Mild frailty according to Fried’s criteria or low handgrip strength (men < 27 kg; women < 16 kg).	○ Recent history of severe fractures or traumatic brain injury (TBI).
○ Timed Up and Go (TUG) test between 10 and 20 s. ○ Falls Efficacy Scale–International (FES-I) score between 20 and 40 points.	○ IMC ≥ 35.
○ Activities-specific Balance Confidence (ABC) Scale score ≥ 67%. ○ Dizziness Handicap Inventory (DHI) score ≥ 30 points. ○ Older adults who have not received interventions aimed at fall prevention or cognitive function stimulation for at least six weeks prior to study enrollment.	○ Decompensated heart disease or uncontrolled cardiac arrhythmias.
○ Provision of written informed consent.	
○ Adequate tolerance to visual and auditory stimuli.	

**Table 2 ijerph-23-00504-t002:** This is a table of Virtual Reality-Based Program for Fall Risk Reduction in Older Adults in Primary Health Care.

Activities/Exercises	Time	Description
Equipment set-up and safety check	−Pre-start to +3 min from session onset	Brief instructions, device adjustment, verification of safe area, and confirmation of participant readiness.
Warm up	5 min.	Use of exercises based on the Fall Prevention Manual for Older Adults and the Wheel within the VIVIFRAIL Program (Categories B, C1, C2, and D)
Balance 1	5 min.	Balance exercises; trunk control exercises, Weight shifting and functional reaching.
Balance 2	8 min.	Balance exercises, trunk control exercises, dynamic balance, locomotion, spatial coordination.
REST/transition	3 min.	Rest.
Balance 3	8 min.	Balance exercises, trunk control exercises, dynamic balance, locomotion, spatial coordination.
Balance 4	5 min.	Balance exercises, trunk control exercises, dynamic balance, locomotion, spatial coordination. Functional mobility.
REST/transition	3 min.	Rest.
Vestibular	8 min.	Vestibular exercises, depending on the needs of the participating older adults.
ADL	5 min.	Daily life-based exercises.
COOL-DOWN	5 min.	Exercises according to the Fall Prevention Manual for Older Adults and VIVIFRAIL program, with emphasis on breathing technique, flexibility, and prevention of cybersickness symptoms.
“Total active intervention time: 60 min including preparation and rest periods.”		

VIVIFRAIL: Multicomponent Physical Exercise Program; Category B: Moderate functional limitation; Category C1: Frail; Category C2: Pre-Frail; D: Autonomous; ADL: Activities of Daily Living.

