**H3:** 
*Older adults receiving the intervention will demonstrate a significant increase in balance-related confidence, as assessed by the Activities-specific Balance Confidence (ABC) Scale, compared with the control group.*

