#### 2.7.4. Virtual Reality-Based Falls Prevention Workshop (Intervention) (Phase 2)

##### VR-Based Program Implementation Sessions

The intervention sessions corresponding to the Virtual Reality Program for Older Adults in Primary Health Care (PHC), aimed at falls prevention, will be implemented in accordance with the guidelines established in the Information Guide for Therapeutic Interventions with Immersive Virtual Reality (INVIRTUE) [33]. The clinical objective of the program is to reduce fall risk and maintain functional capacity within the framework of strategies for preventing functional decline in older adults. The intervention will have a total duration of twelve weeks, with a frequency of two sessions per week and an approximate duration of 60 min per session. The process will be supervised by an interdisciplinary team composed of occupational therapists and speech-language pathologists, who will provide continuous clinical monitoring, personalized feedback, and timely management of any adverse symptoms associated with the use of immersive virtual reality (iVR), such as dizziness, nausea, or disorientation.

Prior to the initiation of the program, an introductory session will be conducted to familiarize participants with the technology. During this session, explanatory audiovisual content will be presented, information regarding the therapeutic objectives will be provided, and a practical demonstration of device use will be performed. Participants’ questions will be addressed, and potential concerns related to the immersive experience will be discussed.

For the deployment of the intervention, appropriate preparation of the physical environment will be essential, ensuring a spacious, safe area free of obstacles. During each session, the instructor will activate the device and establish the necessary connection to project the experience onto an external screen, allowing the remaining group members to observe the activity and participate interactively through verbal feedback.

Subsequently, each participant will directly engage with the immersive virtual reality environments under constant supervision by the professional team, ensuring safety conditions, therapeutic support, and systematic monitoring of intervention tolerance.

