### 3.2. Secondary Outcomes

#### Concern About Falling

*Falls Efficacy Scale–International (FES-I):*

The Falls Efficacy Scale–International (FES-I) was developed to provide a comprehensive measure of concern about falling, incorporating both physical and social factors, while ensuring suitability for cross-cultural applications. Available evidence strongly supports its use in older adult populations [43]. The FES-I consists of 16 items in which participants rate their level of concern about the possibility of falling in different situations, using a scale ranging from 1 (not at all concerned) to 4 (very concerned). A total score greater than 23 is commonly considered indicative of elevated or clinically relevant concern regarding fall risk [44].

In the present study, is expected on experimental group to show a 3-to-6-point reduction in total FES-I scores, with a lower proportion of participants scoring > 23, reflecting a small-to-moderate effect size (d ≈ 0.40–0.60). This improvement would indicate enhanced perceived self-efficacy and reduced activity restriction due to fear of falling [44].

*Activities-specific Balance Confidence (ABC) Scale:*

The ABC questionnaire consists of 16 items and may be self-administered or applied by a trained evaluator. It is a widely used subjective measure designed to assess balance confidence and the degree of fear of falling experienced by an individual when performing various daily activities, such as moving around the home, ascending or descending stairs, getting into or out of a car, or bending down to pick up objects from the floor, among others [45]. Participants rate their confidence in performing each activity without losing balance or becoming unsteady, generating a total score expressed as percentage, with higher values indicating greater balance confidence.

In this study, changes in total ABC score will be analyzed to evaluate the effect of the intervention on balance-related confidence. A value ≥ 67% has been associated with lower fall risk in community-dwelling older adults and will be considered clinically relevant threshold. Improvements in total score, as well as an increase in the proportion of participants reaching value ≥ 67%, will be interpreted as reflecting enhanced perceived safety and functional confidence during activities of daily living. A small-to-moderate effect size (d ≈ 0.40–0.70) is anticipated,

*Short Physical Performance Battery (SPPB):*

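### The ABC score that admits a participant (≥ 67%) is the same score the protocol treats as the lower-risk target, so on this marker everyone starts where the intervention is meant to bring them

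*Protocol article*

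**What the plan says.** Table 1 of the protocol article sets "Activities-specific Balance Confidence (ABC) Scale score ≥ 67" (per cent) among the inclusion criteria. It is a floor; no upper limit is given.

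Section 3.2, under the ABC scale, gives that value a meaning: "A value ≥ 67% has been associated with lower fall risk in community-dwelling older adults and will be considered clinically relevant threshold". It then plans to use it as an outcome: "an increase in the proportion of participants reaching value ≥ 67%, will be interpreted as reflecting enhanced perceived safety". H3 in the Introduction predicts that the intervention group "will demonstrate a significant increase in balance-related confidence" compared with control, and Section 3.2 adds: "A small-to-moderate effect size (d ≈ 0.40–0.70) is anticipated".

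Section 2.7.4 states the purpose: "The clinical objective of the program is to reduce fall risk and maintain functional capacity". The population named in the aim and in H1 is older adults at risk of frailty. The primary measure of fall risk is the TUG, with more than 13.5 s taken as increased risk (Section 3.1). The other relevant entry criteria in Table 1 are TUG 10–20 s, FES-I 20–40, DHI ≥ 30, and mild frailty or low grip strength.

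**The concern.** A responder threshold is informative when people can start below it. Here the entry rule removes everyone who does, so the entry criterion and the outcome description contradict each other about who is in the trial.

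Three things are at stake.

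- The ≥ 67% proportion cannot show the improvement that the protocol says it will interpret.
- H3 is tested only in people who already have fairly high balance confidence, in the top third of the scale.
- Feasibility, tolerance and fall-risk results would be reported for older adults at risk of frailty in primary care, although nobody below 67% was observed. The recruitment rate in Section 2.9.1 divides those who agree by those invited, and eligibility is checked after interest is expressed (Section 2.4). People lost to the ABC bound therefore need not show up in that indicator.

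**Working it through.** **Sample size, to see whether it is touched.** Inputs from Section 2.3: f = 0.25, α = 0.05, power 0.80, correlation 0.5, ε = 1.0, two groups, two time points. For the group × time test, λ = N·f²·m/(1 − ρ) = 34 × 0.0625 × 2 / 0.5 = 8.5 with 1 and 32 degrees of freedom. Power is 0.807 at N = 34 and 0.781 at N = 32, so the stated minimum of 34 reproduces. ABC does not enter this calculation, and nothing below changes it.

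**The ≥ 67% proportion.** Inputs: entry at ABC ≥ 67% (Table 1) and 20 participants per group (Section 2.3).

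- Baseline proportion at or above 67%: 20/20 in each group, 40/40 overall, or 100%.
- Change = post-intervention proportion − 100%, which is at most 0 percentage points.
- The groups could still differ afterwards, but only in how many people fall below 67%. That is maintenance, not the increase described.

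This takes the baseline ABC to be the score that qualifies the participant. Section 2.7.2 supports that: ABC is part of the baseline assessment, and eligibility is confirmed after it.

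**The ABC score itself.** Baseline lies in 67–100, so the largest possible individual gain is 100 − 67 = 33 points, and it is smaller for everyone who enters above 67.

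**Comparison with the neighbouring criteria.**

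| Measure | Entry range (Table 1) | Protocol's own threshold | Can people enter on the unfavourable side? |
|---|---|---|---|
| TUG | 10–20 s | > 13.5 s = increased risk | Yes |
| FES-I | 20–40 | > 23 = raised concern | Yes |
| ABC | ≥ 67%, no upper limit | ≥ 67% = lower risk | No |

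The TUG and FES-I windows straddle their thresholds, so participants can cross them in the good direction. The ABC range begins exactly at its threshold.

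**Illustrations only.** The protocol gives no ABC mean or SD and no correlation with TUG, so every input here is an assumption.

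- *Truncated normal, source ABC mean 60–80, SD 10–20.* The bound excludes about 10–76% of the source population. Those enrolled have mean ABC of about 73–83 and SD of about 5–9.
- *Bivariate normal, TUG mean 12 s, SD 3; ABC mean 70–75, SD 15–20; correlation −0.3 to −0.6.* Among people with TUG 10–20 s, the bound refuses about 34–54%. It refuses 42–73% of those above 13.5 s and 24–43% of the rest. The share above 13.5 s falls from about 41% to 24–36%. With ABC mean 65 or 80, refusal above 13.5 s runs from 29% to 83%.

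The bivariate model ignores the frailty, grip, FES-I, DHI and functional-status criteria that apply at the same time. It also lets ABC exceed 100: at mean 80 and SD 20, about 16% of draws do. It shows a direction under a negative correlation, not a size.

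**The case against.** The strongest reply is that this is a trial in a mild-risk population and the ABC floor belongs to that choice. The stated population is at risk of frailty, not people with low balance confidence. TUG is capped at 20 s and FES-I at 40, and a floor on ABC likewise removes the severe end. Any entry criterion limits generalisability without biasing the comparison among those enrolled. Table 1 gives no rationale for any criterion, and a journal article may leave that to the full protocol.

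Much of this stands. A reader might infer that the trial refuses the higher-risk people it is meant to serve, or that its results would apply only to confident, lower-risk people. The protocol does not support that. Its primary marker of fall risk is TUG, and someone with TUG 15 s and ABC 70% passes both of those criteria. Entry also admits FES-I above 23 and requires DHI ≥ 30 together with mild frailty or low grip. Even the illustrative simulation leaves 24–36% of the sample above 13.5 s. A reader might also infer a smaller effect on H1; nothing in the document shows one.

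Nor is it shown that H3 becomes undetectable. Using the illustrative enrolled SD, d = 0.40–0.70 corresponds to about 0.40 × 4.9 = 2.0 up to 0.70 × 9.1 = 6.4 points, against average headroom of about 100 − 83 = 17 to 100 − 73 = 27 points. Truncation shrinks the SD as well, so the standardised effect need not shrink.

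What the reply does not answer is the clash between Table 1 and Section 3.2. A deliberate mild-risk floor is coherent; planning to read a rise in the proportion above that same floor is not.

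**Conclusion.** The point holds as an internal conflict with a consequence for scope. Table 1 and Section 3.2 use one ABC value both to define entry and to define success. From the text alone, 100% of participants are on the lower-risk side of ABC at baseline, the proportion cannot rise, baseline ABC is restricted to 67–100, individual gain is at most 33 points, and there will be no evidence about people below 67%. The only assumption is that the qualifying score serves as the baseline score.

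The point does not extend to a general exclusion of higher-risk people, to a demonstrated loss on H1, or to any particular refusal rate. The sample size is unaffected.

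**What to change.** Reconcile Table 1 with the ABC paragraph of Section 3.2 in one of two ways.

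1. Revise the ABC entry bound so that it fits the planned use of the ≥ 67% threshold. This is one line in Table 1 and an ethics amendment. The downside is a sample more varied on ABC.
2. Keep the bound, state the reason for it, and drop the ≥ 67% proportion as a sign of benefit, leaving the change in total ABC score. Then word H3 and the feasibility and fall-risk conclusions as applying to older adults who already have ABC ≥ 67%. This costs a few sentences and a narrower stated scope.

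Which entry rule is right is for the trial team to decide. Neither route needs extra visits, staff or participants.

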## Data Availability

Data will be available upon reasonable request from the corresponding author.

## Abbreviations

The following abbreviations are used in this manuscript:

RV	Virtual Reality
APS	Primary Health Care
+AMA	More Independent Seniors Program
EFAM	Functional Assessment of Older Adults
DHI	Dizziness Handicap Inventory
TUG	Timed Up and Go
SPPB	Short Physical Performance Battery
FES-I	Falls Efficacy Scale-International
ABC	The Activities-specific Balance Confidence Scale
SSQ	Simulator Sickness Questionnaire
INVIRTUE	Information Guide for Therapeutic Interventions with Immersive Virtual Reality
VIVIFRAIL	Multicomponent Physical Exercise Program
